**C.5.2 Postpartum intervention schedule and assessments**

After the late pregnancy visit, all women and couples in the intervention arm will be asked to return at 6 weeks and 3 months postpartum and every 3 months thereafter until the end of follow-up at 24 months postpartum or 6 weeks after the end of breastfeeding, whichever occurs first. Women and couples in the control arm will be asked to return at 3 and 6 months postpartum and every 6 months thereafter until the end of follow-up at 24 months postpartum or 6 weeks after the end of breastfeeding, whichever occurs first.

Participants randomized to the intervention arms (Arms I-2 & C-2) will receive enhanced counseling at every visit and will be retested for HIV at 3, 6, 12, 18 and 24 months postpartum (or at the end of follow-up, whichever occurs first). At these visits, both intervention and control women and men participants will undergo a physical examination and will be asked to answer individually a follow-up behavioral questionnaire about their sexual behaviors, relational and reproductive intentions, including family planning. At these same visits, all women will be bled for syphilis and HIV rapid testing and two vaginal swabs will be collected, one for G/C, and Tv testing and the other for Y chromosome detection while a blood or urine sample or urethral swab will be obtained from symptomatic men for syphilis, G/C and Tv testing [*See Schedule of Events, Appendix C*].

At the end of follow-up, all study participants irrespective of their arm assignment will undergo a physical examination, will be asked to answer individually an end-of-study questionnaire and will be bled for syphilis and HIV rapid testing and a vaginal or urethral swab will be collected for G/C and Tv testing. A vaginal swab will also be collected from women to test for the presence of Y chromosomes.

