**C.5.4 Cohort retention methods**

Our study power calculations account for a rate of attrition as high as 50% to ensure sufficient power for the primary endpoint comparisons[[1]](#footnote-2). Given that such a high rate carries a risk of bias, we have put in place strategies to minimize losses to follow-up as follows:

- Participants in the urban or rural site will be carefully assessed at enrolment for their mobility in order to pre-empt selective attrition
- All women and couples consenting to participate will have agreed to home visits by a study field officer.
- At the time of enrollment the field officer will make a home visit and complete a tracking locator form.
- Study retention will be monitored monthly.
- To maximize retention over 24 months of follow-up, study visits have been scheduled to coincide as much as possible with the standard ante-natal or post-natal immunization schedule and additional retention visits have been inserted so that all participants will be on a regular quarterly visit schedule.
- Every participant will be given a free calendar with visits dates marked to help them remember their appointments.
- Trained counselors will maintain regular contact with participants through calls and SMS messages while respecting participants’ schedule and privacy.
- Family and women support groups linked to both Kitgum and Mulago PMTCT programs will also help retain participants in the study by reinforcing prevention messages.
- If a participant misses a follow-up visit, a field officer or a study peer will follow up by phoning as soon as possible to reschedule the visit.
- When needed, the field officer or peer will make a follow-up visit either at the participant’s home or at an agreed upon location.

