**C.7.2 Secondary outcomes**

Secondary outcomes include the incidence of intended and unintended (recurring) pregnancies, maternal and infant mortality rates, and the rate of MTCT of HIV among infants born to mothers who acquired HIV during follow-up. Post-partum pregnancies will be diagnosed clinically or by urine testing. Infants of HIV-infected mothers will be tested for HIV by DNA PCR before 18 months of age or by rapid HIV antibody test at >18 months of age.

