**C.8.3 Secondary analyses**

In calculating incidence of new pregnancies, time-at-risk will start 60 days following delivery. , Incidence of new pregnancies and MTCT will be modeled as HIV incidence above. For MTCT and new pregnancies, and infant and maternal mortality, the unit of analysis will be newborns and women participants, respectively. **Mediating factors:** The intervention is designed to enhance individual reports of partner economic and emotional support and to enhance couples’ levels of communication, mutual support and decision-making. We expect that as individuals and couple’s levels of psychosocial indices increase, they will be more likely to participate in HIV testing, less likely to engage in HIV sexual risk behavior and less likely to acquire STIs. Specifically, we hypothesize that 1) over time, intervention participants will exhibit higher scores on individual and couple-level psychosocial indices; and 2) psychosocial indices will mediate the relationship between intervention and study outcomes (HIV testing, sexual risk behavior, STI infection). **Individual-level analyses:** We will first assess whether intervention assignment impacts individual-level psychosocial variables using longitudinal mixed models. Second, we will assess whether psychosocial indices impact follow-up retention, sexual risk behavior or STI infection. Third, we will assess whether these changes in psychosocial indices mediate the effect of the intervention on subsequent HIV testing, sexual risk behavior and STI infection using the approach of Kenny[48](#_ENREF_48). This approach includes comparing estimates of the effect of the intervention on subsequent HIV testing, sexual behavior and STI infection in models with and without potential mediators. **Dyadic analyses:** In addition to the role of individual-level psychosocial variables on the intervention effect, we will also consider couple-level, (or dyadic) data, looking at actor-partner effects which allow for estimation of the effect of both partners’ psychosocial indices on each other. For example, we will consider the role of a woman’s reported communication on her own outcomes (actor effect) as well as the influence of her male partner’s reported communication on her testing and/or sexual behavior (partner effect). These analyses can be used for both continuous and categorical psychosocial variables. We will examine actor-partner effects for all of the proposed mediating variables on each of the outcomes of interest which will allow us to analyze the role that partners may play in improving the health of each other and their infants.

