***Appendix C (cont’d*) - Summary of events and measurements by study arms and visits**

|  | **Controls** | | **All** | | | **Intervention arm (ERHTEC)** | | |
| --- | --- | --- | --- | --- | --- | --- | --- | --- |
| **Follow-up** | **Standard counseling** | **Standard HIV testing & counseling** | **STI testing** | **Behavioral questionnaire, blood draws + vaginal/urethral swabs** | **Qualitative intervention assessment** | **HIV testing & enhanced counseling** | | **Risk reduction counseling,**  **Infant feeding/nutrition education & Family planning counseling** |
| Formative |  |  |  |  | **X** |  | |  |
| Baseline | **X** | **X** | **X** | **X** |  | **X** | | **X** |
| Late pregnancy | **X** | **X** | **X*** | **X** |  | **X** | | **X** |
| *6 weeks* | ***x*** |  |  |  |  |  | | ***X*** |
| 3 months | **X** | **X** | **X*** | **X** |  | **X** | | **X** |
| 6 months | **X** | **X** | **X*** | **X** |  | **X** | | **X** |
| *9 months* |  |  |  |  |  |  | | ***X*** |
| 12 months | **X** | **X** | **X*** | **X** | **X** | **X** | | **X** |
| *15 months* |  |  |  |  |  |  | | ***X*** |
| 18 months | **X** | **X** | **X*** | **X** |  | **X** | | **X** |
| *21 months* |  |  |  |  |  |  | | ***X*** |
| 24 months**+** | **X** | **X** | **X** | **X** | **X** | **X** | | **X** |
|  |  | **Measurements** | | | | |  | |

 **Retention visits:
-** Participants in the intervention arms will receive enhanced counseling but blood and vaginal swabs or urine samples will not be
 collected unless deemed necessary by the clinician.
- Participants in the control arms will receive standard counseling when study visits correspond to scheduled post-natal visits but
 will not be asked to come back otherwise until their final follow-up visit.
- No questionnaire will be administered during retention visits.

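### The visit schedules conflict between sections, and recurrent pregnancy is not tied to the visits both arms share, so its between-arm comparison can depend on the schedule

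*Protocol*

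**What the plan says.** The protocol describes the postpartum schedule in three places.

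- C.5.2, intervention arm: "all women and couples in the intervention arm will be asked to return at 6 weeks and 3 months postpartum and every 3 months thereafter". Visits stop at 24 months or 6 weeks after breastfeeding ends.
- C.5.2, control arm: "Women and couples in the control arm will be asked to return at 3 and 6 months postpartum and every 6 months thereafter", with the same end point.
- C.5.4: "additional retention visits have been inserted so that all participants will be on a regular quarterly visit schedule".

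The summary table in Appendix C agrees with C.5.2. It shows contacts at 9, 15 and 21 months for the intervention arm only. Its note says that controls, apart from visits that coincide with routine post-natal care, "will not be asked to come back otherwise until their final follow-up visit".

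At these retention contacts the intervention arm receives counselling that includes family planning. No questionnaire is given. On samples, the note reads "Participants in the intervention arms will receive enhanced counseling but blood and vaginal swabs or urine samples will not be" and continues "collected unless deemed necessary by the clinician".

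Physical examinations, behavioural questionnaires, HIV tests and the women's STI tests are set at 3, 6, 12, 18 and 24 months in both arms. For pregnancy, C.7.2 says only: "Post-partum pregnancies will be diagnosed clinically or by urine testing". C.8.3 starts time at risk 60 days after delivery and adds: "Incidence of new pregnancies and MTCT will be modeled as HIV incidence above". In C.8.2 that model is a pooled logistic regression with robust standard errors and inverse-probability weights for dropout.

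**The concern.** A pooled logistic model compares the odds of an event per person-interval. It is fair between arms only if the intervals are equally long and the event is equally likely to be noticed in each. HIV meets both conditions. Recurrent pregnancy need not, because nothing ties its diagnosis to the shared visits, and the extra intervention contacts deal with family planning.

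Two distortions could follow, in opposite directions. More contacts can reveal more pregnancies, namely those that end early or whose mother is lost before the next half-yearly control visit. Shorter intervals, if they become the rows of the model, lower the odds per row in the intervention arm.

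Unintended recurrent pregnancy is the first-listed secondary outcome, and planning later pregnancies is one of the three behaviours the intervention promotes. The weights are also affected. C.5.7 withdraws participants who miss more than two consecutive scheduled visits. After month 6, three missed visits span 3 × 3 = 9 months on the intervention schedule and 3 × 6 = 18 months on the control schedule.

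**Working it through.** **1. Count the visits (C.5.2, Appendix C).**

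| | Intervention | Control |
|---|---|---|
| Planned postpartum contacts | 6 weeks, 3, 6, 9, 12, 15, 18, 21, 24 months = 9 | 3, 6, 12, 18, 24 months = 5 |
| Of these, after day 60 | 8 | 5 |
| With examination, questionnaire and HIV test | 5 | 5 |

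The 6-week visit (day 42) falls before time at risk starts. So does the control counselling that Appendix C marks at 6 weeks. The plan's own figure is reproduced: C.8.5 counts 7 assessments including baseline, and baseline + late pregnancy + 5 = 7 in each arm. The primary outcome is therefore measured on equal schedules.

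**2. Interval length, by hand.** Assume a constant conception rate from month 2, pregnancies visible from half a month after conception, diagnosis possible at every contact, no losses and no true effect. Both arms then record about the same number of pregnancies.

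- One row per attended visit: 8 rows against 5, so the odds ratio is about 5/8 = 0.63.
- Stratified by visit, only shared visits contribute. The conception window captured at months 3, 6, 12, 18 and 24 is 0.5 + 3 + 6 + 6 + 6 = 21.5 months for controls and 0.5 + 3 + 3 + 3 + 3 = 12.5 months for the intervention arm. The ratio is 12.5/21.5 = 0.58.

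**3. Simulation under no true effect (400,000 women per arm).** These assumptions are not in the protocol: 10 or 20 conceptions per 100 woman-years; 0, 15 or 25% of pregnancies ending at 1 to 4 months and not recalled later; diagnosis possible at every contact. Loss to follow-up is 0 or 50% over 24 months (C.7.1 puts the 50% at 2 years, C.8.5 at 18 months). Ranges cover the two conception rates.

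| Early endings | Loss | Detected, intervention/control | OR, common intervals | OR, one row per visit | OR, stratified by visit |
|---|---|---|---|---|---|
| 0 | 0 | 1.00 | 1.00 | 0.63 | 0.58 |
| 0 | 50% | 1.03–1.04 | 1.02–1.04 | 0.67–0.68 | 0.61–0.62 |
| 15% | 0 | 1.05–1.06 | 1.05–1.06 | 0.67 | 0.62 |
| 15% | 50% | 1.07–1.08 | 1.08 | 0.70–0.71 | 0.64–0.65 |
| 25% | 0 | 1.07–1.08 | 1.08–1.09 | 0.68–0.69 | 0.64 |
| 25% | 50% | 1.11 | 1.11–1.12 | 0.72–0.73 | 0.66–0.67 |

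The first row matches the hand calculation.

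**4. Shared visits only.** With both arms ascertained at 3, 6, 12, 18 and 24 months, the detection ratio is 0.99–1.01 in every scenario.

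**5. Size against sampling error (410 women per arm).** SE of the log ratio ≈ √(1/e₁ + 1/e₀).

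- 10 conceptions per 100 woman-years, 25% early endings, 50% loss: 410 × 0.1007 = 41.3 and 410 × 0.0907 = 37.2 pregnancies, SE 0.23. Excess detection: ln 1.11 = 0.10, about 0.5 SE. Interval effect: ln 0.72 = −0.33, about 1.5 SE.
- 20 conceptions per 100 woman-years, no early endings, 50% loss: 410 × 0.2029 = 83.2 and 410 × 0.1975 = 81.0 pregnancies, SE 0.16. Excess detection: ln 1.027 = 0.03, about 0.2 SE. Interval effect: ln 0.67 = −0.40, about 2.6 SE.

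These counts are of all pregnancies. Unintended ones alone would be fewer and the SE larger.

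**The case against.** A reader might infer that pregnancies are diagnosed at 9 visits in one arm and 5 in the other, and that the comparison is therefore biased. The documents do not support this. Nine against five counts contacts, not diagnostic visits. Planned examinations and questionnaires are 5 against 5, and the default at retention contacts is no sample and no questionnaire. Giving every contact full power to diagnose is a worst case.

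The odds ratios of 0.6 to 0.7 are not a consequence of the plan as written either. They need one row per arm-specific visit and no term for interval length. Modelling pregnancy in the same way as HIV can fairly be read as using the common HIV intervals, and then this artefact disappears. Building person-intervals is ordinary detail for an analysis plan, which may exist.

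The excess detection is also modest. A continuing pregnancy outlasts a six-month gap, everyone has a final assessment, and C.5.4 provides tracing by phone or home visit after a missed visit.

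All of this limits the size of the concern. It does not remove it. A clinical diagnosis needs neither questionnaire nor sample, a new pregnancy would naturally come up in family planning counselling, and nothing excludes such diagnoses from the analysis. An analysis plan could define the intervals. It could not settle whether controls have quarterly contacts, or recover pregnancies that controls were never asked about.

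**Conclusion.** The conflict between C.5.4 on one side and C.5.2 with Appendix C on the other is plain and must be reconciled. The protocol also leaves the ascertainment of recurrent pregnancy open, so the comparison can be biased in a direction that the text does not fix.

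If every contact can diagnose, the worst case is about 0 to 11% more pregnancies detected in the intervention arm. This is about zero without early losses or dropout, and small against sampling error. If each arm's own visits form the intervals without a term for length, the odds ratio is roughly 0.6 to 0.7 with no true effect, which is large enough to mislead. Both figures rest on assumed conception, pregnancy-loss and dropout rates, and the simulation ignores follow-up that ends early because breastfeeding stops. That bias will occur is not shown. The primary outcome is not affected. The change is worth making because it is cheap and part of it concerns data collection.

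**What to change.** 1. Reconcile C.5.4 with C.5.2 and Appendix C on whether controls have contacts at 9, 15 and 21 months.
2. In C.7.2, ascertain pregnancy in the same way in both arms at 3, 6, 12 and 18 months and at the final visit. Ask about any pregnancy since the last shared visit, including one that has ended, and use the urine test already available.
3. In C.8.3, assign every pregnancy to the common intervals between shared visits in the pooled logistic model.
4. Define remaining in follow-up for the weights on the same shared visits.
5. Report pregnancies known only from intervention-arm retention contacts separately, with a sensitivity analysis including and excluding them. A rule that counts a pregnancy only if the woman attends the closing shared visit would discard confirmed events on a condition that arises after randomization. It should be a sensitivity analysis at most.

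The cost is protocol wording, one standard question and a urine test at visits that already take place; C.3.3 already trains counsellors in pregnancy testing. No visits or participants are added. The downside is that a few pregnancies seen only at retention contacts leave the main comparison.

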In this study, we will test the hypothesis that 1) extended repeat HIV testing and enhanced counseling (ERHTEC) in late pregnancy (>36 weeks of gestational age) and throughout breastfeeding can increase and sustain risk reduction behaviors and prevent incident sexually-transmitted infections (ST)I and HIV infections among HIV-uninfected pregnant women, and 2) that couple HTC can further enhance this effect through improved couple communication and emotional and economic support from male partners. We will conduct a stratified randomized trial in Mulago, Kampala and St Joseph Kitgum hospitals in Uganda. The intervention will consist in providing HIV-negative pregnant women enrolled individually or in couples extended repeat HIV testing and enhanced counseling (ERHTEC) in late pregnancy (>36 weeks) and at 3, 6 12, and 18 months postpartum. ERHTEC will emphasize reinforced risk reduction behavior centered around the concept of ensuring an HIV-free and healthy baby and family. The comparison group will receive repeat standard HTC in late pregnancy and standard counseling during follow-up.

The specific aims of the study are:

Aim 1: to assess the effect of ERHTEC on sexual risk behavior and STI and HIV acquisition in HIV-uninfected pregnant and lactating women enrolled individually

Aim 2: to assess the effect of ERHTEC on sexual risk behavior and the incidence of STIs and HIV in uninfected pregnant and lactating women enrolled with their partner, and

Aim 3: to assess the costs and estimate the cost-effectiveness of the intervention.

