# PROTOCOL SUMMARY

**Background**

**Design**

This study consists in a stratified randomized trial, a qualitative formative component at baseline, a qualitative assessment at end of follow-up, and a cost-effectiveness analysis.

Formative research qualitative component**:** Focus Group Discussions (FGDs) will be conducted at baseline to explore knowledge, beliefs, attitudes, challenges and expectations about primary HIV prevention among pregnant and lactating women and their partners.

Stratified randomized trial component**:** A stratified randomized trial will be conducted to compare an extended HIV repeat testing and enhanced counselling (ERHTEC) intervention aimed at preventing HIV acquisition in pregnant and lactating women to the current Ministry of Health recommendation to retest and counsel HIV-uninfected women in late pregnancy (>36 weeks).

End of follow-up qualitative assessment: FGDs and key informant interviews (KIIs) will be conducted at end of follow-up to assess the acceptability and feasibility, barriers and facilitators of the ERHTEC intervention

Additional research components:

Cost-effectiveness of the ERHTEC intervention

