**Study outcomes**

Formative research outcomes:

Perceptions, attitudes, expectations and potential barriers about men involvement in (MNCH care, and an ERHTEC intervention.

Primary outcomes for the randomized trial

Comparison of unprotected sex frequency, and HIV and STI incidence rates among intervention (ERHTEC) and control (standard WHO recommendation) arms .

Cost-effectiveness of the ERHTEC intervention compared to standard of care

Secondary outcomes for the randomized trial

Comparison of unintended recurrent pregnancy rates across study arms

Associations of individual and dyadic variables with the primary and secondary outcomes

Maternal and infant mortality rates

Additional study outcomes

Trial participants’ and staff’s experiences and perceptions about the intervention

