**C. DESIGN AND METHODS**

**C.1 Study Design**

We will conduct a stratified randomized trial of 820 HIV-negative pregnant women and 410 male partners in Mulago Hospital in Kampala and St Joseph District Hospital in Kitgum, Northern Uganda: in each site 205 women enrolled individually and 205 couples will be randomized to be retested and counseled either in late pregnancy (>36 weeks) only as per the WHO/MOH recommendation, or to receive the ERHTEC intervention throughout pregnancy and breastfeeding as follows:

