### C.4.6 Randomization

There are four study arms:

| Individual Arm 1 (Arm I-1) | HIV-negative pregnant women enrolling **without** their partner and who will receive standard HIV retesting and counseling in late pregnancy only |
| --- | --- |
| Individual Arm 2 (Arm I-2) | HIV-negative pregnant women enrolling **without** their partner and who will receive the ERHTEC intervention in late pregnancy AND throughout breastfeeding as described below (C.5 Follow-up) |
| Couple Arm 1  (Arm C-1) | HIV-negative pregnant women enrolling **with** their partner and who will receive standard HIV retesting and counseling in late pregnancy only |
| Couple Arm 2 (Arm C-2) | HIV-negative pregnant women enrolling **with** their partner and who will receive the ERHTEC intervention in late pregnancy AND throughout breastfeeding as described below (C.5 Follow-up) |

Enrolled women and couples will be randomized to either the control (repeat HTC in late pregnancy [>36 weeks] only), or to the ERHTEC intervention. Prior to the study onset, four sets of randomized, sequentially numbered lists of participants identification numbers (IDs) will be prepared by the statistician at UCSF. The randomization lists will be computer-generated using random-sized block groups and will include consecutive intervention numbers with corresponding random intervention assignments. Randomization lists will be encrypted in password-protected files, backed up on computer and the UCSF server and emailed to the MU-JHU Data Center in Kampala. Sealed copies of the original randomization list and documentation of the procedure used to generate the lists will be stored in the project administrative offices in San Francisco and Kampala. Each enrolment number will be preceded with a code letter indicating the trial group (“I” for individual, “F” for the female partner of a couple, “M” for the male partner of a couple) and followed by a randomization allocation code (“E” for ERHTEC intervention, “C” for control) and a site code (“KA” for Kampala, “KI” for Kitgum).. At randomization, MU-JHU Data Center will issue randomization numbers to the study coordinators based on the order of enrollment at each site and on the participants’ group allocation (individual or couple).

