**- Blood draw + vaginal swab**

**- Follow-up questionnaire**

**- ERHTEC HIV & STI TC**

**POST-NATAL VISITS**

**- ERHTEC (counseling only):**

**Infant feeding**

**Risk reduction**

**Family planning**

**- Blood draw + vaginal swab**

**- Follow-up questionnaire-**

**- Repeat standard HTC**

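### The control is defined as HIV retesting in late pregnancy only, but control women are tested on the same dates as the intervention arm, so the trial cannot show what extended retesting does in women

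*Protocol*

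**What the plan says.** Several places define the control by a single retest. C.1 has controls "retested and counseled either in late pregnancy (>36 weeks) only as per the WHO/MOH recommendation". C.4.6 describes both control arms as women "who will receive standard HIV retesting and counseling in late pregnancy only". The Protocol Summary (Design) compares ERHTEC "to the current Ministry of Health recommendation to retest and counsel HIV-uninfected women in late pregnancy (>36 weeks", and its list of outcomes makes the comparison "among intervention (ERHTEC) and control (standard WHO recommendation) arms". The Abstract states: "The comparison group will receive repeat standard HTC in late pregnancy and standard counseling during follow-up". It names no postpartum retest for controls.

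The schedule differs. C.5.1 gives every woman a late-pregnancy retest. C.5.2 brings control women back at 3 and 6 months and then every 6 months, which are the dates on which the intervention arm is retested. It then says: "At these same visits, all women will be bled for syphilis and HIV rapid testing". In the Appendix C flow chart for women, five control boxes read "Repeat standard HTC". The Appendix C summary table has a control column "Standard HIV testing & counseling", marked on every row where the intervention arm has HIV testing.

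The last paragraph of the Abstract says that the findings will inform national policy on what retesting during pregnancy and breastfeeding does for primary HIV prevention.

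**The concern.** The intervention is named for two components, extended retesting and enhanced counseling. The stated control would differ from it on both. The scheduled control differs only in the content of the counseling and in the number of counseling visits. For women, the retesting component is the same in both arms.

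What is at stake is the reading of the result. A null result could be taken to mean that extended retesting does not help, although the controls received it. A positive result could be credited to retesting. C.8.5 invites this by calling the intervention arms the repeat HTC arms. The policy sentence in the Abstract rests on a contrast that the schedule does not contain.

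There is a conditional consequence for C.8.4. It costs testing on the WHO schedule and on the trial's repeat schedule, while infections averted are estimated from sexual behavior observed in the trial. If controls were costed on the WHO schedule, the costs and effects would refer to different comparators.

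**Working it through.** **1. The plan's own figure.** C.8.5 states 80% power for a 10% reduction, two-sided 5%. Its inputs are 410 women and 410 couples, 7 assessments, correlation 0.3, baseline 5 episodes, over-dispersion 2, a 30% control-arm reduction and 50% loss. I inverted the summed X'WX as C.8.5 describes, with power = Φ(|ln 0.9|/SE − 1.96) and |ln 0.9| = 0.1054. Loss was assumed to reach 50% at the last assessment.
- Linear loss: SE 0.0369, power 81.4%.
- Constant-hazard loss: SE 0.0374, power 80.3%.

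The stated 80% is reproduced. No input refers to the HIV test schedule, so power does not depend on this point.

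**2. Follow-up HIV tests per woman.** The enrolment test is left out because it establishes eligibility.

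| Date | Intervention | Control as scheduled | Control as defined in C.1 and C.4.6 |
|---|---|---|---|
| Late pregnancy (C.5.1) | 1 | 1 | 1 |
| 3 months (C.5.2) | 1 | 1 | 0 |
| 6 months | 1 | 1 | 0 |
| 12 months | 1 | 1 | 0 |
| 18 months | 1 | 1 | 0 |
| 24 months or end of follow-up | 1 | 1 | 0 |
| Total | 6 | 6 | 1 |

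The total agrees with C.8.5: 7 assessments including baseline, 7 − 1 = 6. The five control boxes in the Appendix C chart cover late pregnancy to 18 months. The sixth test is the final assessment, which C.5.2 requires irrespective of arm.

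**3. Early end of follow-up.** If follow-up ends at month T, each arm has 1 + (number of 3, 6, 12, 18 below T) + 1 tests. At T = 13 this is 1 + 3 + 1 = 5 in both arms. The difference is 0 for every T.

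**4. Distance from the stated definition.** 6 − 1 = 5 tests per control woman. With 205 + 205 = 410 control women, that is at most 410 × 5 = 2,050 tests beyond the defined control. This maximum assumes no loss and no early end of follow-up.

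**5. Incremental tests per woman in C.8.4.**
- Controls costed as delivered: 6 − 6 = 0.
- Controls costed on the WHO schedule: 6 − 1 = 5.

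**6. Related text.**
- Control men: C.5.2 names no HIV test at 3, 6, 12 and 18 months. The Appendix C chart for men lists standard HTC in five control boxes, and with the final test that makes 6. Its footnote limits the symptomatic-only rule to STI samples.
- Final assessment: in both charts, women and men, the two final boxes read ERHTEC, whereas the summary table gives controls standard testing and counseling at 24 months.

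**The case against.** The strongest defence is that HIV incidence is a primary outcome (C.7.1), so both arms must be tested on the same dates, and the extra control tests are measurement. The first half stands: equal test dates are right, and I do not suggest removing them. The second half does not. Appendix C labels the control tests as testing with counseling, so control women receive the testing component as a service.

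A second defence is that hypothesis 1 and Aims 1 and 2 concern ERHTEC as a package and claim no separate effect of retesting. That also stands. A reader might infer that the randomized comparison is invalid, the power wrong, or the aims in need of restatement. The documents support none of these: the package comparison remains randomized and testable, and step 1 reproduces the power.

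A reader might also infer that the C.8.4 analysis is wrong. It is only ambiguous. The same section says that costs will be measured for the intervention and comparison arms, and C.7.5 collects actual expenditure at each site, which points to costing as delivered. But the C.8.4 reference to the WHO schedule and the C.7.5 label for the control type leave the other reading open.

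Finally, a reader might infer that control men go untested between late pregnancy and the final visit. C.5.2 is silent on them rather than contradictory, and it refers to Appendix C, which supplies the tests.

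**Conclusion.** The control definition is wrong as written. Control women are scheduled for the same HIV tests as intervention women, at most 6 versus 6, where the definition implies 1 versus 6. The trial therefore cannot estimate, for women, the effect of extended retesting against the WHO/MOH schedule, and the closing policy sentence of the Abstract is not supported as worded. The effect that it can estimate in women is that of enhanced counseling and additional counseling visits versus standard counseling, with retesting held equal.

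The count rests only on C.5.1, C.5.2 and Appendix C, and loss or early weaning does not change the equality of the schedules. The cost mismatch of 5 tests per woman with no matching effect contrast arises only if controls are costed on the WHO schedule. This should be fixed, but it is a correction of wording and interpretation and not of the design.

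**What to change.** - **Control definition.** In the Abstract, the Protocol Summary (Design and Study outcomes), C.1 and C.4.6, state that control women receive standard HIV testing and counseling on the same dates as the intervention arm.
- **Policy sentence.** Limit the end of the Abstract to the effect of enhanced counseling and additional counseling visits versus standard counseling under the same retesting schedule, and interpret the ERHTEC effect in women that way. Hypothesis 1 and Aims 1 and 2 need no restatement.
- **C.8.4.** State that testing is costed as delivered in each arm, in line with that section's own sentence on the costs of both arms. Label any late-pregnancy-only WHO comparator as a modelled scenario.
- **Consistency.** State control men's HIV tests in C.5.2 in line with Appendix C. Correct or clarify the control final-assessment boxes in both Appendix C charts.

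The cost is protocol wording and a narrower claim about retesting. Enrolment, randomization, sample size and the primary model do not change.
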